## Abstract

**Background:**

Bisphosphonates can reduce fracture risk in patients with osteoporosis, but many at-risk patients do not start or adhere to these medications. The aims of this study are to: (1) preliminarily evaluate the effect of an individualized 10-year osteoporotic fracture risk calculator and decision aid (*OSTEOPOROSIS CHOICE*) for postmenopausal women at risk for osteoporotic fractures; and (2) assess the feasibility and validity (i.e., absence of contamination) of patient-level randomization (vs. cluster randomization) in pilot trials of decision aid efficacy.

**Methods/Design:**

This is a protocol for a parallel, 2-arm, randomized trial to compare an intervention group receiving *OSTEOPOROSIS CHOICE *to a control group receiving usual primary care. Postmenopausal women with bone mineral density T-scores of <-1.0, not receiving bisphosphonate therapy, and receiving care at participating primary care practices in and around Rochester, Minnesota, USA will be eligible to participate in the trial. We will measure the effect of OSTEOPOROSIS CHOICE on five outcomes: (a) patient knowledge regarding osteoporosis risk factors and treatment; (b) quality of the decision-making process for both the patient and clinician; (c) patient and clinician acceptability and satisfaction with the decision aid; (d) rate of bisphosphonate use and adherence, and (e) trial processes (e.g., ability to recruit participants, collect patient outcomes). To capture these outcomes, we will use patient and clinician surveys following each visit and video recordings of the clinical encounters. These video recordings will also allow us to determine the extent to which clinicians previously exposed to the decision aid were able to recreate elements of the decision aid with control patients (i.e., contamination). Pharmacy prescription profiles and follow-up phone interviews will assess medication start and adherence at 6 months.

**Discussion:**

This pilot trial will provide evidence of feasibility, validity of patient randomization, and preliminary efficacy of a novel approach -- decision aids -- to improving medication adherence for postmenopausal women at risk of osteoporotic fractures. The results will inform the design of a larger trial that could provide more precise estimates of the efficacy of the decision aid.

**Trial registration:**

Clinical Trials.gov Identifier: NCT00578981

## Background

The societal burden associated with osteoporotic fractures is already great[1], but is expected to increase further with aging of the population [2]. Randomized trials have conclusively shown that use of bisphosphonate therapy in postmenopausal women can reduce their risk of osteoporotic fractures. Postmarketing studies have established a favorable balance of benefit over harms [3]. Limited start and adherence to bisphosphonates in at-risk patients, however, reduces this beneficial impact [4-7]. When bisphosphonates are prescribed, about 50% of patients discontinue therapy within one year of its prescription [8,9]. Given current estimates of the prevelance of at-risk people -- the National Osteoporosis Foundation estimates that 44 million people in the United States age 50 years or over have either osteoporosis or osteopenia [10] -- the potential morbidity, mortality and expense associated with bisphosphonate nonadherence is significant.

Poor adherence appears related, in part, to undisclosed and unexplored patient values and preferences [11,12], as well as gaps in patient understanding of the efficacy and safety of pharmacologic treatment [13]. One way to facilitate patient understanding and to elicit patient preferences is to use decision aids in consultations. Decision aids are tools that help patients participate in choosing among management options by providing them with information about the relevant features of the available choices. A systematic review of 55 randomized trials of decision aids vs. usual care, pamphlets, or education revealed that, overall, decision aids are effective at improving knowledge acquisition and reducing so-called decisional conflict (i.e., uncertainty about the choice, ignorance about the pros and cons of each option, pressure to make a particular choice, and effectiveness of the decision) [14]; their effect on medication adherence remains largely unknown.

To our knowledge, our group has produced the only randomized trial evidence supporting improvements in adherence to preventive medications, using a decision aid about statins in patients with type 2 diabetes [15]. In this case, clinicians and patients found the tool, *Statin Choice*, acceptable; and, compared with no intervention, patients receiving the decision aid had more knowledge about and more accurate expectations of potential benefits and harms of statin use. They also reported significant reductions in decisional conflict and showed a 3-fold increase in the odds of self-reported adherence to statins at 3 months.

The timing for *OSTEOPOROSIS CHOICE *has coincided with a paradigm shift in the management of osteoporosis [10]. The prior standard approach relied most heavily on bone mineral density (BMD) results as measured with dual-energy X-ray absorptiometry (DXA) to inform practice guidelines and treatment decisions [16,17]. While BMD T-scores can identify high risk patients, they are both insensitive and nonspecific [18] since they do not address other pertinent factors related to risk of fracture [19]. Moreover, the actual probability of experiencing an osteoporotic fracture with any given T-score is not immediately evident or available [20]. With the arrival of FRAX, the World Health Organization's calculator of 10-year osteoporotic fracture risk [21], treatment recommendations can now be commensurate with the probability of a hip fracture or any major osteoporotic fracture (hip, spine, distal forearm, humerus). FRAX risk estimates are based on population-based cohort studies. These studies generated models that incorporate a patient's BMD at the femoral neck, when available, and clinical risk factors. These factors include age, sex, ethnicity, body mass index, personal and parental history of prior osteoporotic fracture, long term use of oral glucocorticoids, rheumatoid arthritis or other secondary causes of osteoporosis (e.g. type 1 diabetes, premature menopause, chronic malabsorption, hyperthyroidism, hypogonadism), and current alcohol and tobacco use [19]. Current osteoporosis practice guidelines incorporate the use of FRAX [10], but optimal use of this tool is still evolving [20].

At the onset of this project, the best available decision aid for osteoporosis treatment was 35 pages long [22], did not incorporate absolute fracture risk estimates, and its efficacy remained unexplored. In contrast, *OSTEOPOROSIS CHOICE*:

• is a one page, paper-based decision aid;

• incorporates a specific patient's 10-year risk of an osteoporotic fracture estimated using the FRAX online calculator http://www.shef.ac.uk/FRAX/; and

• is designed for use between patients and their clinicians.

The aim of this study is to evaluate the effect of an individualized fracture risk calculator and decision aid for postmenopausal women at risk of osteoporotic fractures, *OSTEOPOROSIS CHOICE*, on knowledge transfer, the quality of the decision making process, and on patient adherence to medications. Given our choice of study design, i.e., randomization at the patient level, we also will seek to evaluate the potential for contamination and poor fidelity in the use of the decision aid in this setting. Here we present the protocol we are using to conduct this trial.

## Methods

### Design

To evaluate the decision aid, we propose to conduct a patient-level multicenter randomized trial. The Mayo Clinic Institutional Review Board approved all study procedures.

### Setting

Patients and primary care clinicians for this trial are to be recruited at 10 practice sites affiliated with the Mayo Clinic, all located in Southeastern Minnesota within a 60-mile radius of Rochester, Minnesota, USA.

### Participants

#### Inclusion criteria

Eligible clinicians include physicians, physician assistants and nurse practitioners at participating sites. Eligible patients include postmenopausal women, age 50 and over who have BMD levels consistent with a diagnosis of low bone mass (osteopenia) or osteoporosis, who are not taking bisphosphonates or other prescription osteoporosis medications to treat low bone mass (other than vitamin D and calcium), whom their clinicians find eligible for bisphosphonate therapy and have a follow-up appointment with their clinician, and who are available for a telephone follow-up 6 months after randomization.

#### Exclusion criteria

*The trial will exclude *women who cannot read English or have, in their clinicians' judgment, major learning barriers such as visual or hearing impairment or dementia that would compromise their ability to give written informed consent (or use the decision aid).

#### Participant recruitment

We will identify eligible women from DXA lists and from participating clinicians' appointment calendars. If there were no pre-scheduled follow-up appointments after the BMD evaluation, we will request participating clinicians schedule such an appointment to discuss abnormal BMD results with the patient during an office visit, not via a telephone conversation. The study coordinator will inform patients about the trial, confirm their eligibility, and obtain written informed consent in a private room at the clinic site. Patients will be offered 15 dollars in compensation for time spent completing study procedures.

### Interventions

#### Decision aid

The *OSTEOPOROSIS CHOICE *decision aid tool was developed through an iterative process and with extensive field-testing involving patients, clinicians, designers, and researchers [23,24]. This one-page decision aid provides the patient's individualized 10-year risk estimate of having a major osteoporotic fracture (clinical spine, forearm, hip or shoulder fracture). The risk is calculated using data from the patient's medical record (completed by direct query to patient or clinician as needed) and entering it into the online FRAX tool as implemented during the course of the study.

We developed three decision aids that describe the pros and cons of treatment, one for each of three categories of estimated 10-year risks of fracture: <10%, 10-30%, and >30%. At the time we designed the decision aids, there were no guidelines to orient therapeutic decisions based on fracture risk. Thus, the design team, in conjunction with patients and clinicians, arbitrarily chose these thresholds. The decision aid also shows the patient-specific absolute reduction of fracture risk with alendronate, assuming a treatment-related reduction in overall osteoporotic fracture risk of 40% [25], and the potential downsides of taking bisphosphonates.

To estimate the gastrointestinal side effects of oral bisphosphonates we reviewed the FDA-approved package insert, reports of pivotal clinical trials, and observational studies [3]. Evidence of the association between bisphosphonate use and osteonecrosis of the jaw was also evolving while we were designing the tool [26]. The estimate presented was derived from available reviews of weak evidence and expert judgment from specialist clinicians on our research team [27]. Finally, the decision aid also prompted further discussion of these issues with the question "What would you like to do? (Figure 1).

**Figure 1 F1:**
[figure not shown]
**Osteoporosis Choice decision aid for a patient with a 10-year fracture risk of 20%**.

In the intervention arm, a study coordinator will review with the clinician the patient's tailored *OSTEOPOROSIS CHOICE *decision aid tool immediately prior to the clinician's visit with that patient. The clinician and the patient will then review the decision aid together in the context of their clinical encounter. This procedure, which is similar to one used in our prior decision aid trial in primary care [28], has the advantages of being time-sensitive and incorporates as-needed just-in-time training in the use of the tool. We have found that clinicians delivering decision aids during the visit yield somewhat superior results (e.g. significantly improved knowledge transfer) to researchers delivering the tool prior to the visit [29].

#### Usual care

In the usual care arm, the clinician will discuss the patient's BMD test results and options for treatment in that clinician's usual fashion, i.e., with no other research-related intervention. The patient will receive the National Osteoporosis Foundation booklet, "Boning Up On Osteoporosis: A Guide To Prevention and Treatment."

### Randomization

A computer-generated allocation sequence will randomize patients 1:1 in a concealed fashion to control (usual care + booklet) or intervention (*OSTEOPOROSIS CHOICE *decision aid). The study coordinator will complete the following steps:

• assess the eligibility of the patient, obtain the patient's written informed consent and enroll the patient;

• access a secure study website, input patient identifiers to document patient eligibility;

• obtain from the website interface the arm of the study to which the patient is allocated;

• when the website is not available, the coordinator will contact the study statistician and a similar procedure will be used to provide concealed random allocation.

After randomization, only data analysts will remain blind to allocation. If a patient were suspected of having incorrectly enrolled, e.g., the patient is found to be ineligible after enrollment and randomization, the study coordinator will present the case to the study principal investigator ([name]) for consideration. Following existing recommendations [30], the principal investigator will decide on exclusion while unaware of any consequences of enrollment, including the patient's allocation or outcomes.

The following issues were considered in our choice[15] to randomize clinics, clinicians, or patients:

• *Randomize by clinics *- This approach would enable us to train everyone in the intervention (and control) clinics to use (or not) the decision aid. Disadvantages included the small number of available clinics, difficulty in balancing the number of participating clinicians and patients across sites, and limited ability to avoid selection bias or implement allocation concealment.

• *Randomize by clinicians *- This approach would enable clinicians to develop skills for using the decision aid, and resolve any confusion related to when each clinician should use or not use the decision aid. Unfortunately, in our judgment, these advantages did not outweigh the inability to implement allocation concealment, the residual potential for selection bias, and the potential for a large imbalance of numbers of patients per clinician that could emerge [15]. Because of the relatively small number of participating clinicians, clinician charisma or communication skills could confound the results of the effect of the decision aid. Finally, there could be a potential risk of recruitment and randomization of clinicians with few or null eligible or enrolled patients during the trial.

• *Randomize by patients *- This approach would enable allocation concealment and avoid selection bias. However, it opens the study to the potential for contamination at the clinician level; it is difficult logistically to determine when a clinician will use the decision aid or not (and therefore expedite recruitment in a busy practice setting); and it slows the learning curve that may exist when clinicians adapt to using the decision aid in practice.

Because the design was simple and we placed a high value in avoiding bias, we implemented this third approach. The main disadvantage of patient randomization is clinician contamination. Contamination in this case refers to a clinician who, having used the decision aid with a prior patient, is able to recreate elements of the decision aid with a subsequent patient allocated to receive usual care. We use the term 'recreate' given that clinicians will not have access to the decision aid when seeing patients not allocated to the intervention arm. We recognize that clinicians could produce these elements by drawing from their own knowledge base, i.e., not true contamination, so to this extent this assessment may overestimate the rate of contamination.

Since we did not find a published approach to determine the extent to which this design could introduce contamination, we developed a "contamination checklist" with which to judge how clinicians will present information about osteoporosis risk and treatment effect of bisphosphonates in video recordings of the clinical encounters (see below). The tool checks for clinicians' use of 12 key elements of the decision aid (Additional File 1) when seeing a control patient. A score of 12 in a control visit with a clinician who has previously used the decision aid would indicate maximum contamination (note that a score of 12 in an intervention patient would indicate maximum fidelity in delivering the decision aid). Given the small sample size and number of clinicians likely to enroll more than one patient, only a few instances of potential contamination (i.e., control patients visit with a clinician who has had a decision aid visit previously) are likely to take place. Therefore, our analyses will be limited to descriptions of the distribution of overall scores and the frequency of each item.

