• Additional questions (see appendix) inquire about the treatment decision made during the visit and patient satisfaction with the degree of participation in the decision-making process.

The clinicians' survey, to be completed after each study visit, includes questions regarding which decision the patient made, the clinician's confidence in the patient's understanding of the information offered, and the clinician's prediction of patient action (start and adherence to bisphophonates at 6 months).

To evaluate the quality of decision-making, we will use the OPTION scale [33] on the video recordings. This scale allows an observer to quantify the extent to which clinicians are able to involve patients in the decision-making process. We have used the OPTION scale on video-recorded encounters with adequate reliability in previous studies [28,34]. Video recordings also provide information about encounter duration (using the video time stamps), fidelity of use of the tool, and difficulties and successes experienced while using the decision aid, and are the source of data for the contamination checklist described above.

We will use two methods to assess patient adherence to bisphophonates at six months. We will contact patients by telephone and measure patient self-reported adherence using the Haynes' single item adherence question ("Have you missed any of your pills in the last week?") a measure associated with a 96% specificity and 75% accuracy vs. a pill count standard [35,36]. We will also obtain patients' pharmacy records in order to objectively determine medications filled since the study visit. Using this information, we will consider a gap (time without medication) of longer than 90 days as bisphosphonate discontinuation. We will assess adherence to bisphosphonates by assessing the proportion of days covered during the 180 days after the visit, taking into account potential overlap in supply that may result when a refill comes before the estimated completion of the previous fill. We will define persistence as the number of days from the first prescription fill to the last fill in the 180 days after the visit. In this case, we will take into account overlapping supply and the number of days supplied at the last fill, truncating at 180 days after the visit [37,38]. In addition to these continous measures, we will assess and compare the proportion of patients who exhibited ≥ 80% adherence to bisphosphonates in both groups.

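### Blinding is confined to data analysts: nothing withholds a clinician's earlier use of the aid from the contamination raters, or the arm from the 6-month caller

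*Protocol article*

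**What the plan says.** The masking rule is one sentence in the Randomization section of the protocol article: "After randomization, only data analysts will remain blind to allocation". The same paragraph contains one narrow exception. When a patient may have been enrolled in error, "the principal investigator will decide on exclusion while unaware of any consequences of enrollment, including the patient's allocation or outcomes".

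Three outcomes are obtained through a person who could know the arm or the clinician's history:

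- **Contamination checklist** (Randomization). The team built a 12-element tool "with which to judge how clinicians will present information about osteoporosis risk and treatment effect of bisphosphonates in video recordings of the clinical encounters". Its meaning depends on context: "A score of 12 in a control visit with a clinician who has previously used the decision aid would indicate maximum contamination", whereas the same score in an intervention visit means full fidelity. On analysis, "our analyses will be limited to descriptions of the distribution of overall scores and the frequency of each item".
- **OPTION scale** (Outcomes and data collection), also scored from video: "This scale allows an observer to quantify the extent to which clinicians are able to involve patients in the decision-making process".
- **Self-reported adherence at 6 months** (Outcomes and data collection): one fixed question, put to the patient by telephone.

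The article does not say who rates the videos, in what order, or who makes the calls.

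**The concern.** The abstract names two aims, and the second is whether patient-level randomization is valid in the sense of being free of contamination. The checklist is the only instrument described for it. If raters know which control visits were conducted by clinicians who had already used the aid, their expectation can raise or lower the score in exactly the visits that answer the question. The conclusion could be wrong in either direction: false reassurance that patient-level randomization is safe, or a false signal that a larger trial needs clusters.

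The stake in the telephone call is smaller. The patient gives the answer, but a caller who knows the arm can affect how the question is put, probed or recorded.

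The article says that patient-level randomization was chosen because avoiding bias was highly valued. Masking these two steps serves the same purpose.

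**Working it through.** No figure in the documents decides this point, so the check is a reading of the relevant sections side by side.

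1. **What the rule covers.** The word *only* makes it a statement about everyone else, so a rater or caller who is not a data analyst is not blind to allocation. The exception for the principal investigator concerns exclusions and produces no outcome data. No other section masks a rater or caller.

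2. **Which fact matters for contamination.** There are two, and they differ:
   - *Allocation of the patient on the video.* The rule addresses this. In an intervention visit the aid is in use during the recording, so a rater will usually recognise the arm.
   - *Whether the clinician in a control visit had used the aid before.* The rule does not address this. Clinicians have no access to the aid in control visits, so the recording need not reveal it.

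3. **How a rater could learn of prior use.** The article leaves several routes open:
   - The same checklist serves as the fidelity score in intervention visits. A rater who has already scored a clinician's intervention visit knows that this clinician has used the aid.
   - Visit date or sequence would allow it to be inferred.
   - Under Randomization and Interventions, the study coordinator obtains the allocation and reviews the aid with the clinician just before each intervention visit. If a coordinator also rated videos or made calls, the information would already be known. The article does not say that this happens.

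4. **How a rating reaches the result.** The maximum score is 12 for 12 elements, which implies one point per element. One element called differently in one visit moves that visit's score by 1/12 = 8.3% of the scale. With *k* exposed control visits, it moves the frequency of that element by 1/*k*. The article expects only a few such visits, so *k* is small, and the analysis is descriptive. The raw ratings are therefore the result.

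5. **Why unexposed control visits matter.** The Randomization section concedes that clinicians may supply the same elements from their own knowledge, so the score may overstate contamination. Control visits by clinicians who have not yet used the aid are the natural reference for that background level. Setting the two groups beside each other is credible only if raters cannot tell them apart.

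6. **What can be masked.** Prior use can be withheld for control videos, provided that the rater has not yet seen intervention videos. The arm can be left off the call list. The arm cannot realistically be hidden from someone rating an intervention video.

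**The case against.** The strongest reply is that a condensed article gives a one-line summary of masking and leaves rating and call procedures to the full protocol or a manual. This disposes of any complaint that details are absent. It does not dispose of the point, because the article states who is blind and limits that group. If the full protocol does mask raters or callers, the sentence is inaccurate and still needs amending.

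Several stronger readings are tempting, and the documents do not support them:

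- *Raters know which clinicians were exposed.* Nowhere is this said. The blinding sentence concerns patient allocation. What can be said is that nothing withholds prior use.
- *Adherence is scored by an unblinded judge.* The question is fixed and the patient answers it. The risk is influence on a self-report.
- *Pharmacy adherence is compromised too.* The article says "We will also obtain patients' pharmacy records in order to objectively determine medications filled since the study visit" and sets rules for gaps, overlapping supply and truncation. No finding is made there, and these records give a second adherence measure that does not depend on the caller.
- *The bias could never be undone.* Recordings can be rated again under masking if they are kept.
- *Prior use can be hidden completely.* It cannot be hidden from a rater who has already scored that clinician's intervention visits, so the order of rating is part of the remedy.

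It is also fair to say that this is a 100-patient pilot and that no formal test of contamination is planned. That limits the consequences. It does not protect the contamination result, since a descriptive summary of a few visits depends wholly on the ratings.

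**Conclusion.** The point holds in a limited form. The plan keeps only data analysts blind, apart from the principal investigator's exclusion decisions. It does not withhold prior use of the aid from the checklist raters, or the arm from the 6-month caller. The consequence is greatest for the contamination aim, which has no other instrument, and smaller for self-reported adherence, which has pharmacy records beside it.

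The documents do not allow the bias to be sized. They give neither the number of exposed control visits nor any measure of rater or caller influence, and the direction could be either way. The conclusion assumes that raters and callers are not the blinded data analysts, and that no masking beyond the article's sentence is in force. It is an avoidable weakness that merits a change of wording and procedure. It does not show that the ratings will be biased.

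**What to change.** Amend the blinding statement in the Randomization section so that:

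- **(a)** control-visit videos are scored on the contamination checklist before the rater sees any intervention video, in random order, with visit date, sequence and the clinician's prior use of the aid withheld;
- **(b)** the 6-month call uses the fixed question from a call list that omits the arm, made where feasible by existing staff who were not at that woman's visit;
- **(c)** OPTION and fidelity ratings of intervention visits are reported as unavoidably unblinded and interpreted accordingly.

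The cost is protocol wording, a shuffled video list and a call list without the arm column. Recruitment and visits are unaffected. There are two small downsides: a rater must finish the control videos before starting the intervention videos, and calls need some scheduling. Patients know what they received and may mention it on the telephone, so (b) reduces the risk without removing it.

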An important reason to run feasibility trials of decision aids designed for use in clinical practice is that these tools could directly impact the content and duration of the consultation in favorable or unfavorable ways. When clinicians at multiple sites with different interests and priorities see eligible patients, they may not perceive the need to use the decision aid for this particular decision, may not find it appropriate for use in some patients, and may not use the decision aid appropriately [40]. Thus, an evaluation of the feasibility of the decision aid aided by video recording of as many visits as possible provides a rich database to ascertain these challenges. Results may lead to process modifications in trial design, revised criteria for selection of clinicians and patients, or changes in the decision aid itself, prior to a larger efficacy study. These insights will also affect efforts to implement effective decision aids in practice [41,42].

In conclusion, the *OSTEOPOROSIS CHOICE *trial is designed to provide initial empirical evidence of feasibility and efficacy of a novel approach -- decision aids -- to improve adherence to medication for patients with osteoporosis. We will also seek to assess the feasibility and effect on validity of patient-level randomization as an alternative to cluster randomization at the clinician and clinic level in preliminary studies of decision aid efficacy. The results will inform the design of a larger trial that could provide more precise estimates of the efficacy of the decision aid.

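### The contamination rule covers only a clinician's own earlier aid visit, so it cannot inform carry-over between colleagues at one site, which the randomization-level aim needs

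*Protocol article*

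**What the plan says.** The Randomization section defines the term: "Contamination in this case refers to a clinician who, having used the decision aid with a prior patient, is able to recreate elements" of the aid with a later usual-care patient. When it introduces the 12-item checklist it repeats the limit twice. It reads the top score this way: "A score of 12 in a control visit with a clinician who has previously used the decision aid would indicate maximum contamination". It describes instances of potential contamination as "control patients visit with a clinician who has had a decision aid visit previously". The checklist itself is described more broadly, as looking for the 12 elements "when seeing a control patient". The analysis is confined to describing total scores and item frequencies.

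The same section notes that clinicians may produce these elements from their own knowledge, and concludes that "to this extent this assessment may overestimate the rate of contamination". No route to underestimation is mentioned.

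The Abstract equates validity of patient-level randomization with absence of contamination. The Discussion says this design is to be assessed "as an alternative to cluster randomization at the clinician and clinic level in preliminary studies of decision aid efficacy".

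**The concern.** The rule recognises one kind of exposure, the same clinician's own earlier aid visit. The intervention is a single paper page, both arms run side by side at the same 10 practices, and colleagues at a practice may talk. If a colleague of an aid user reproduces elements of the aid in a control visit, that visit falls outside potential contamination whatever its score.

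This matters because of what the pilot is meant to inform. If carry-over stays within the clinician, randomizing clinicians would remove it. If it passes between colleagues, only randomizing clinics would. A rule that looks only within the clinician cannot help a later trial choose between the two.

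A second, smaller problem is that the exposure is worded in three ways that are not equivalent. The difference matters for a clinician who has an aid visit but does not use the aid, which the Discussion expects may happen.

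**Working it through.** **Wordings side by side**

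- Abstract, Methods/Design: clinicians earlier *exposed* to the aid.
- Randomization, definition: clinicians who have *used* the aid with a prior patient.
- Randomization, checklist paragraph: clinicians who have *had an aid visit* ("control patients visit with a clinician who has had a decision aid visit previously"), though the sentence on the maximum score again refers to use.

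A clinician who is briefed, has the visit and sets the sheet aside is exposed under the first and third wordings but not under the second. None of the three mentions a same-site colleague's visit.

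**How many control visits could be involved**

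The protocol gives no count of exposed control visits, so there is no figure to reproduce. What follows is an illustration.

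Inputs from the protocol: 100 women (Statistical considerations), 1:1 allocation (Randomization), so 50 controls, and 10 sites (Setting).

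Assumed: 10 women per site, random order, and the number of clinicians, which is not stated.

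*Earlier aid visit at the same site.* A control visit preceded by j women at its site has no earlier aid visit with probability 0.5^j. Averaging over positions:

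1 − (1/10) × Σ(j=0..9) 0.5^j = 1 − 1.998/10 = 0.80, or about 40 of 50. About 50 − 40 = 10 control visits precede any aid visit at their site.

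*Earlier aid visit by the same clinician*, with exactly m women each, is 1 − (1/m) × Σ(j=0..m−1) 0.5^j:

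- m = 2: 1 − 1.5/2 = 0.25, or 12.5 of 50.
- m = 5: 1 − 1.9375/5 = 0.6125, or 30.6 of 50.

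The difference, exposed at the site but outside the rule, is 40 − 30.6 ≈ 9 to 40 − 12.5 ≈ 28 of 50.

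*Simulation.* Here the number of women per clinician varies by chance, with K clinicians spread over 10 sites and either equal or skewed expected loads. Mean control visits out of 50:

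| K | Own visit, equal | Colleague only, equal | Own visit, skewed | Colleague only, skewed |
|---|---|---|---|---|
| 20 | 32 | 9 | 36 | 5 |
| 40 | 22 | 18 | 28 | 13 |
| 60 | 16 | 24 | 22 | 18 |
| 80 | 13 | 27 | 19 | 21 |
| 100 | 11 | 30 | 17 | 24 |

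The two columns of each pair sum to about 40 to 41, in line with the closed form. The colleague-only count runs from about 5 to 30. It rises as women per clinician fall, and Statistical considerations expects that ratio to be very low.

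**The case against.** Several stronger readings are tempting, and the text does not support them.

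- *Visits outside the rule are treated as uncontaminated.* The checklist is described for control patients in general, so these visits appear to be scored and described. They are only not labelled potential contamination.
- *Contamination is undercounted, or an unexposed baseline is spoiled.* The figures above count co-location in time and place, not transfer of content. No exposed-versus-unexposed comparison is planned, so there is no baseline to spoil.
- *The coordinator's briefing is a separate missed route.* It takes place "immediately prior to the clinician's visit with that patient", in the intervention arm only, so a briefed clinician normally goes straight into an aid visit and falls within the checklist paragraph's wording. What remains is the case of an aid visit without use.
- *Clinicians from development are in the trial.* The aid was developed "with extensive field-testing involving patients, clinicians, designers, and researchers", but the article does not say whether those clinicians or their practices take part. Overlap is possible but not shown.

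It is also fair to say that clinicians have no access to the aid in control visits, that each sheet is tailored to one patient, and that nothing documents transfer between colleagues. The analysis is only descriptive, and a split by site could be added later.

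These objections remove the stronger claims and lower the priority. They do not change the fact that the rule has no place for a same-site colleague, that the three wordings differ, or that the acknowledged bias runs in one direction only.

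**Conclusion.** The point holds in a limited form. The protocol labels a control visit as potential contamination only through that clinician's own earlier aid visit and acknowledges only overestimation. As written, the rule cannot inform the choice between clinician-level and clinic-level randomization, although the stated aim covers both.

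The size is illustrative: roughly 5 to 30 of 50 control visits with same-site exposure outside the rule, assuming 20 to 100 clinicians, 10 equal sites, 1:1 allocation and random order. The lower figures need about five women per clinician, which fits poorly with the very low ratio that the protocol expects. A reader might infer that contamination will be missed on this scale. The documents support possible exposure only, and whether any content passes between colleagues is unknown. This is an optional refinement to a descriptive analysis and does not undermine the trial.

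**What to change.** 1. Use one exposure definition throughout: an earlier aid visit by the clinician, whether or not the aid was actually used. Reconcile the Abstract and both places in Randomization with it.
2. Report the planned checklist totals and item frequencies for all recorded control visits at three levels: the clinician's own earlier aid visit; an earlier aid visit by a same-site colleague only; none known.
3. If any trial clinician took part in field-testing, class that clinician as previously exposed.
4. State that contamination may be underestimated as well as overestimated.

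The cost is a merge of visit order, site and clinician from data already held, plus one question per clinician about earlier contact with the aid. The drawback is that the level with no known exposure will be small, about 10 visits in the illustration, and early in calendar time. It can serve only as an imprecise descriptive reference.
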